### Intervention

2.6

Participants in both groups will receive lifestyle intervention during the 16-week intervention period. According to previous evidence from reproductive medicine (27–29), participants will be encouraged to adopt a balanced diet, engage in moderate physical activity suited to individual capacity, and maintain regular work and rest schedule. They will also be advised to avoid smoking, limit alcohol consumption. We designed a healthy lifestyle adherence scoring to assess adherence (see Supplementary S2 File). Lifestyle adherence will be assessed weekly throughout the 16-week intervention period using the Healthy Lifestyle Adherence Scoring System, which includes four domains: dietary modification, physical activity, sleep–wake regulation, and avoidance of harmful substances. Each domain will be scored from 0 to 2, with a total weekly score ranging from 0 to 8. Deviations from lifestyle recommendations will be documented during follow-up assessments.

#### Intervention group

2.6.1

Participants in the intervention group will receive a standardized YYRM therapy once weekly for 16 weeks. All treatments will be administered in a fixed treatment room equipped with a dedicated moxibustion smoke purification and local exhaust device (Hubei Aite Environmental Purification Technology Co., Ltd., Hubei, China) (Figure 3). This therapy alternates between prone and supine positions, with moxibustion applied to specific body regions based on traditional meridian theory.

**Figure 3 fig3:**
[figure not shown]
Fixed two-bed treatment room for Yin-Yang Regulating Moxibustion. The room is equipped with dedicated moxibustion smoke purification and local exhaust devices to provide standardized environmental control during treatment.

In the prone position, treatment is centered on the Mingmen acupoint (GV4), covering an approximate 8–10 cm radius. In the supine position, moxibustion targets the Shenque acupoint (CV8) (Figure 4). The two positions alternate weekly throughout the intervention (GV4 on Week 1, CV8 on Week 2, and so on). The alternating CV8/GV4 treatment schedule will be implemented according to a predefined protocol. CV8 and GV4 were selected as complementary core acupoints according to the TCM therapeutic principle of warming yang and tonifying the kidney, which corresponds to the kidney yang deficiency pattern commonly described in DOR.

**Figure 4 fig4:**
[figure not shown]
The procedure of Yin-Yang Regulating Moxibustion. A compressed moxa disc is positioned on top of the ginger base at Shenque (CV8) or Mingmen (GV4).

At the beginning of each session, the practitioner molds a ginger paste disc approximately 3 cm thick (around 700 g in weight and 10 cm in diameter) using a circular mold and places it over the selected acupoint. A compressed moxa disc (14.5 cm in diameter, approximately 30 g) is then positioned on top of the ginger base and ignited. Each treatment lasts for 40 min. Throughout the session, the practitioner monitors the local skin temperature using a digital thermometer with a probe, maintaining a stable temperature between 40 °C and 44 °C. If the temperature rises above the target range or causes discomfort, a clean cotton pad is inserted between the ginger and the skin to reduce heat. To reduce smoke-related exposure, the smoke purification and local exhaust device will be operated throughout all moxibustion sessions, with routine room ventilation maintained as needed (30, 31). If a participant reports discomfort related to moxa smoke, the practitioner will promptly adjust the local ventilation conditions. At each session, the practitioner will record the participant’s treatment position, acupoint, treatment duration, temperature range, and any deviations from the planned procedure to ensure consistency and feasibility of the 16-week YYRM intervention. All treatments are performed by licensed Traditional Chinese Medicine practitioners trained specifically in YYRM methodology. The detailed procedure is provided in Supplementary S3 File.

#### Control group

2.6.2

The control group will receive weekly lifestyle intervention sessions over the same period, covering dietary guidance, lifestyle modification, emotional management, and avoidance of environmental toxins. No moxibustion interventions will be administered to the control group.

### Outcome measurement

2.7

#### Primary outcome

2.7.1

AFC: At baseline (week 0), after the 16-week intervention (week 16) and at the end of the follow-up period (week 32), transvaginal ultrasound examinations will be performed to assess the number of 2–9 mm antral follicles in both ovaries. The total AFC will be calculated as an important indicator of ovarian reserve function.

#### Secondary outcomes

2.7.2

(1) Serum levels of AMH, FSH, LH: At baseline (week 0), after the 16-week intervention (week 16) and at the end of the follow-up period (week 32), venous blood samples will be collected during the early follicular phase (days 2–4 of the menstrual cycle) to measure AMH, FSH, and LH levels (32, 33).

(2) Scale Assessments: The following validated scales will be used to assess outcomes: Modified Kupperman Index (mKMI) (34): To evaluate the severity of menopausal symptoms. Hamilton Anxiety Scale (HAMA) (35) and Hamilton Depression Scale (HAMD) (36): To assess the effects of the intervention on anxiety and depressive symptoms. Menopause-Specific Quality of Life Questionnaire (MENQOL) (37): To assess health-related quality of life during the perimenopausal period. Assessments will be conducted at week 0, week 16, and week 32.

#### Safety assessment

2.7.3

Adverse events (AEs) will be recorded throughout the intervention and follow-up periods. At each treatment visit, participants will be asked about any AEs they may have experienced. For each reported AE, the following information will be documented: specific symptom(s), onset time, duration, severity, resolution time, and the suspected relationship to the intervention. Particular attention will be paid to potential AEs associated with moxibustion, including those caused by heat or moxa smoke exposure. Commonly reported moxibustion-related adverse effects may include local burns, blisters, skin itching, dizziness, eye swelling, foot pain, dry mouth, constipation, and abdominal pain (38).

#### Rs-fMRI

2.7.4

Resting-state functional magnetic resonance imaging (rs-fMRI) will be conducted at Hubei Provincial Hospital of Traditional Chinese Medicine. Each participant will undergo two MRI scans, at baseline (week 0) and after the 16-week intervention (week 16). For each participant, longitudinal MRI scans will be scheduled at a similar time of day whenever possible to minimize circadian-related variability in resting-state neural activity. Relevant pre-scan lifestyle factors, including sleep status, caffeine and alcohol intake, smoking status, and vigorous physical activity, will be recorded and considered when interpreting rs-fMRI findings. Before scanning, participants will be instructed to remove all metallic objects and wear noise-reducing earplugs. During scanning, participants will lie in a supine position, remain still, and keep their eyes closed while staying awake and relaxed. Foam cushions will be used to fix the head in place to minimize motion artifacts. This study will collect multimodal neuroimaging data to investigate the potential mechanisms by which the intervention modulates brain function and structure.

All imaging will be performed on a Siemens MAGNETOM Skyra 3.0 T MRI scanner using a 32-channel head coil. The imaging protocol includes a high-resolution T1-weighted structural sequence, rs-fMRI and diffusion weighted images (DWI) sequence. To exclude intracranial structural abnormalities that may interfere with the results, anatomical evaluation will be performed concurrently.

Scanning Parameters: High-resolution T1-weighted structural imaging (T1WI): Acquisition time = 280 s matrix = 256 × 256 × 176 slices, repetition time (TR) = 2000 ms, echo time (TE) = 2.23 ms, flip angle = 8°, field of view (FOV) = 240 × 240 × 240, voxel size = 0.9 × 0.9 × 0.9 mm. fMRI scan: acquisition time = 488 s, matrix = 64 × 64 × 36 slices, TR = 2000 ms, TE = 30 ms, dynamic scans = 240, flip angle = 90°, FOV = 224 mm × 224 mm × 224 mm, voxel size = 3.5 mm × 3.5 mm × 4.0 mm. DWI: acquisition time = 945 s, matrix = 112 × 112 × 46 slices, TR = 6,600 ms, TE = 107 ms, FOV = 224 mm × 224 mm × 224 mm, voxel size = 2.0 mm × 2.0 mm × 3.0 mm. A multi-shell protocol was used with b-values of 0, 1,000, and 2000.

Consistent with prior human resting-state fMRI studies investigating hypothalamus-centered functional connectivity (39), a standardized preprocessing and analysis pipeline will be implemented to mitigate the influence of limited spatial resolution and physiological noise. Preprocessing will include removal of the initial volumes to ensure signal stabilization, slice timing correction, rigid-body head motion correction, and spatial co-registration of functional images to the corresponding high-resolution T1-weighted structural images, followed by normalization to standard space. To further reduce non-neuronal signal contributions, nuisance regression will be performed, including signals derived from white matter, cerebrospinal fluid, and motion parameters. Temporal band-pass filtering will be applied to retain low-frequency fluctuations relevant to resting-state functional connectivity, while attenuating high-frequency physiological noise. Spatial smoothing will be conducted using a modest Gaussian kernel to enhance signal-to-noise ratio while preserving anatomical specificity in subcortical regions.

Hypothalamus-centered seed regions will be defined based on established anatomical references in standard space. In accordance with prior human rs-fMRI studies, seed locations will be placed within the medial and lateral hypothalamic regions using standardized MNI coordinates reported in the literature (e.g., medial hypothalamus approximately at *x* = ±4, *y* = −2, *z* = −12; lateral hypothalamus approximately at *x* = ±8, *y* = −10, *z* = −12), with small spherical regions of interest to minimize contamination from adjacent cerebrospinal fluid and surrounding structures. Seed placement will be further constrained by anatomical masks derived from structural images to ensure consistency across participants.

### Sample size estimation

2.8

The sample size was calculated based on the primary outcome, namely the change in AFC from baseline to week 16. Data from our previous study indicated that the mean AFC level after YYRM treatment in the intervention group was 4.16 ± 0.86, while the change in the waitlist group was 3.00 ± 1.69. Assuming a minimal clinically important difference of 1.8 between the two groups, with a one-sided significance level of *α* = 0.025 and statistical power of 90% (*β* = 0.10), the required sample size was estimated to be 56 participants (28 per group). Considering a potential dropout rate of 15%, the final sample size was increased to 66, with 33 participants in each group. Sample size estimation was performed using PASS15.

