### Statistical analysis

2.9

All data from enrolled participants will be collected and analyzed. Descriptive statistics will be used to summarize baseline characteristics. The Shapiro–Wilk test will be applied to assess the normality of continuous variables. For normally distributed quantitative data, results will be presented as mean ± standard deviation (SD). For non-normally distributed data, results will be presented as median and interquartile range (IQR). Categorical variables will be expressed as frequencies and percentages, and between-group comparisons will be made using the chi-square test or Fisher’s exact test, as appropriate. To assess the treatment effects over time, linear mixed-effects models will be used to analyze repeated measures, accounting for both fixed effects (group, time, group × time interaction) and random effects. Both intention-to-treat (ITT) and per-protocol (PP) analyses will be conducted. For the ITT analysis, missing data will be handled using the Last Observation Carried Forward (LOCF) method, as previously used in acupuncture studies (40, 41). The PP analysis will include participants who complete the intervention and outcome assessments without major protocol deviations. Statistical significance will be defined as a two-sided *p*-value <0.05. All statistical analyses will be performed using SPSS version 24.0.

Lifestyle adherence scores will be summarized during the 16-week intervention period. The mean weekly adherence score will be calculated for each participant based on the Healthy Lifestyle Adherence Scoring System. Between-group differences in lifestyle adherence will be evaluated descriptively. Where appropriate, the mean lifestyle adherence score will be included as a covariate in adjusted analyses for clinical outcomes and rs-fMRI-related exploratory analyses. Sensitivity analyses may also be conducted to examine whether the main findings remain robust after accounting for lifestyle adherence or excluding participants with marked lifestyle non-compliance.

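### The stated difference of 1.8 follicles does not yield 28 per group with the quoted SDs, and the planning inputs mix a post-treatment level with a change

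*Protocol article*

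**What the plan says.** All the figures are in section 2.8 (Sample size estimation) of the protocol article.

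- Endpoint: "The sample size was calculated based on the primary outcome, namely the change in AFC from baseline to week 16".
- Intervention-arm input from the sponsor's previous study: "the mean AFC level after YYRM treatment in the intervention group was 4.16 ± 0.86".
- Control-arm input from the same study: "the change in the waitlist group was 3.00 ± 1.69".
- Design difference: "Assuming a minimal clinically important difference of 1.8 between the two groups".
- Error rates: "with a one-sided significance level of *α* = 0.025", and 90% power.
- Result: "the required sample size was estimated to be 56 participants (28 per group"), raised to 66 (33 per group) for 15% dropout, computed in PASS15.

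Section 2.9 (Statistical analysis) sets the test level: "Statistical significance will be defined as a two-sided *p*-value <0.05". No other SD for antral follicle count (AFC) appears in the article.

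**The concern.** There are two separate faults in one paragraph.

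First, a sample size should follow from the difference, SDs, alpha and power given beside it, and this one does not. A reader will take the trial to have 90% power for a clinically important difference of 1.8 follicles. If it was in fact sized on a smaller difference, the 1.8 has no role in the design, and the reader cannot tell which number the result should be judged against.

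Second, the endpoint is declared to be a change, but one arm's input is described as a level after treatment and the other's as a change. A level in one arm minus a change in the other is not a treatment effect on any endpoint. At least one label must be wrong, and until that is settled the variance behind the power statement is not known to be the variance of what will be analysed.

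**Working it through.** **Inputs (section 2.8).** SDs 0.86 and 1.69; means 4.16 and 3.00; stated difference 1.8; one-sided alpha 0.025 (z = 1.960); power 90% (z = 1.2816); 1:1 allocation; dropout 15%.

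**Pooled SD.** √((0.86² + 1.69²)/2) = √1.798 = 1.341.

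**Formula.** Normal approximation: n per group = 2 × (1.960 + 1.2816)² × SD² / d² = 2 × 10.507 × 1.798 / d². The t-test figures use the noncentral t distribution with equal variances.

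**Step 1: try to reproduce 28 from the stated difference.** For d = 1.8, n = 37.78 / 3.24 = 11.66, so 12 per group. The t test gives 13 and Welch gives 14. The larger SD alone (1.69) gives 19 (normal) or 20 (t). Inflating for a Mann–Whitney test gives about 14 to 16. Relaxing to one-sided alpha 0.05 or 80% power lowers n further. None of these reaches 28.

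**Step 2: what SD would make 1.8 and 28 agree?** Normal approximation: SD = 1.8 × √14 / 3.2415 = 2.08. The t test gives 2.04. Both exceed 0.86 and 1.69.

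**Step 3: look for the difference that does give 28.** The quoted means differ by 4.16 − 3.00 = 1.16. Then n = 37.78 / 1.3456 = 28.08. Rounded up this is 29, and the t test needs 30, so the match to 28 is close but not exact.

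**Step 4: power with 28 per group, pooled SD 1.341.**

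| Difference | Normal approximation | t test | Welch |
|---|---|---|---|
| 1.8 | 99.9% | 99.9% | 99.8% |
| 1.16 | 89.9% | 88.9% | 88.5% |

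**Step 5: dropout.** 28 / 0.85 = 32.9, so 33 per group and 66 in total. This step is correct.

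**Step 6: sidedness.** One-sided 0.025 and two-sided 0.05 share the critical value 1.960, so sections 2.8 and 2.9 agree and sidedness does not explain the mismatch.

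**Step 7: level versus change.** Suppose both SDs are SDs of levels (an assumption; the article does not say). With equal variances and baseline-to-week-16 correlation rho, the SD of the change is 1.341 × √(2(1 − rho)). Power for a 1.16 difference in change, 28 per group, t test:

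| rho | SD of change | Power |
|---|---|---|
| 0.2 | 1.70 | 71% |
| 0.3 | 1.59 | 77% |
| 0.4 | 1.47 | 83% |
| 0.5 | 1.34 | 89% |
| 0.6 | 1.20 | 94% |
| 0.7 | 1.04 | 98% |

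Power falls below the nominal figure for rho under about 0.5 and exceeds it above. For a difference of 1.8, power is at least 97% across this range.

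**The case against.** The strongest reply is that the size is not shown to be inadequate. If 1.8 is the real target, the quoted SDs give more power than claimed. If 1.16 is the target, 28 per group gives about 89%, close to the stated 90%. The dropout step is right, and the Discussion already calls the findings preliminary. All of that stands, and it makes this a fault in the stated basis of the sample size rather than a case for more participants.

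A reader might also conclude that the trial was certainly sized on 1.16 and that 1.8 played no part. The article does not support that as fact. It never states 1.16, and 1.16 gives 28 only if 28.08 is rounded down. Another route is conceivable: if 1.69 were an SD of levels and rho about 0.27 (both assumptions), the SD of the change would be 1.69 × √(2 × 0.73) = 2.04, and 1.8 would then need 28 by the t test. Nothing in the text indicates that this was done. The figure 1.16 remains the likelier source, but only the sponsor can confirm it.

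Finally, one might object that differences well below 1.8 could reach significance: about 0.72 at 28 per group with SD 1.34. That is true but mostly generic, since any trial with 90% power has a significance threshold below its design difference. With 13 per group for 1.8 the threshold would be about 1.09. This point adds little.

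**Conclusion.** Section 2.8 is wrong as written and should be corrected before results are available. On the quoted SDs, 1.8 needs 12 to 13 per group, less than half the 28 reported. The stated N cannot be reproduced from the stated difference under any standard variant tried. It is nearly reproduced by 1.16, the likely but unconfirmed basis. Separately, the inputs are labelled as different quantities, so the SD of the declared endpoint is not established.

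The power figures of about 99.9% (for 1.8) and 89% (for 1.16) rest on 28 evaluable women per group and on 1.34 being the right SD. The 71% to 98% range rests on the further assumption that both SDs describe levels, and on the choice of rho; the article gives no basis for choosing within it. A reader might infer that the trial is underpowered. The article does not support that for 1.8, and for 1.16 the answer depends on an SD of change that is not reported.

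**What to change.** Rewrite section 2.8 in this order.

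1. State which difference sized the trial.
2. From the previous study, give the mean and SD in both arms of the same quantity as the week-16 endpoint, and correct the level and change labels accordingly.
3. Recompute, and state the power that 28 evaluable women per group deliver for that difference. If 1.16 and SD 1.34 are confirmed as the right quantities, that is about 89%. If correcting a label alters the mean or the SD, use the new values instead.
4. Either remove the 1.8, or keep it only as the benchmark against which the week-16 estimate and its confidence interval will be read. In the latter case say that the trial was not sized on it, if that is confirmed.

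The cost is one paragraph reworded and recomputed. The stated power may become slightly less favourable. Whether 66 remains sufficient should be read from the recomputed figure and not assumed beforehand.

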### Statistical analysis

2.9

All data from enrolled participants will be collected and analyzed. Descriptive statistics will be used to summarize baseline characteristics. The Shapiro–Wilk test will be applied to assess the normality of continuous variables. For normally distributed quantitative data, results will be presented as mean ± standard deviation (SD). For non-normally distributed data, results will be presented as median and interquartile range (IQR). Categorical variables will be expressed as frequencies and percentages, and between-group comparisons will be made using the chi-square test or Fisher’s exact test, as appropriate. To assess the treatment effects over time, linear mixed-effects models will be used to analyze repeated measures, accounting for both fixed effects (group, time, group × time interaction) and random effects. Both intention-to-treat (ITT) and per-protocol (PP) analyses will be conducted. For the ITT analysis, missing data will be handled using the Last Observation Carried Forward (LOCF) method, as previously used in acupuncture studies (40, 41). The PP analysis will include participants who complete the intervention and outcome assessments without major protocol deviations. Statistical significance will be defined as a two-sided *p*-value <0.05. All statistical analyses will be performed using SPSS version 24.0.

Lifestyle adherence scores will be summarized during the 16-week intervention period. The mean weekly adherence score will be calculated for each participant based on the Healthy Lifestyle Adherence Scoring System. Between-group differences in lifestyle adherence will be evaluated descriptively. Where appropriate, the mean lifestyle adherence score will be included as a covariate in adjusted analyses for clinical outcomes and rs-fMRI-related exploratory analyses. Sensitivity analyses may also be conducted to examine whether the main findings remain robust after accounting for lifestyle adherence or excluding participants with marked lifestyle non-compliance.

fMRI data will be processed using MATLAB R2017b in conjunction with the CONN functional connectivity toolbox (version 20). Standard preprocessing procedures will include slice timing correction, realignment, spatial normalization to MNI space, smoothing, artifact detection, linear trend and covarients removal, and temporal band-pass filtering. Hypothalamus and other relevant brain regions will be defined as the primary region of interest (ROI) for functional connectivity analysis.

To explore the association between central functional connectivity changes and peripheral ovarian reserve-related biomarkers, an exploratory correlation analysis will be performed. For participants with available imaging and peripheral biomarker data at both baseline and week 16, changes in hypothalamus-centered functional connectivity values will be calculated and correlated with changes in AFC, FSH, and LH from baseline to week 16. Pearson correlation analysis will be used when the variables are normally distributed, whereas Spearman rank correlation analysis will be applied for non-normally distributed variables. When multiple functional connectivity clusters or multiple peripheral biomarkers are examined, appropriate multiple-comparison correction will be applied to adjust for multiple comparisons. These analyses will be considered exploratory and hypothesis-generating, and will not be interpreted as evidence of causal brain-ovary regulation.

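### The repeated-measures model in section 2.9 has no baseline AFC term and does not name the week-16 comparison the trial was sized on as its deciding test

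*Protocol article*

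**What the plan says.** Three parts of the protocol article bear on how the primary outcome is tested.

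- **Section 2.9, Statistical analysis.** The model is introduced with "To assess the treatment effects over time, linear mixed-effects models will be used to analyze repeated measures" and specified as "accounting for both fixed effects (group, time, group × time interaction) and random effects". Baseline AFC is not among the terms, and no visit or contrast is named as deciding the primary outcome. The only covariate mentioned is the mean lifestyle adherence score, to be used where appropriate. The significance level is two-sided 0.05.
- **Section 2.7.1, Primary outcome.** AFC is measured at baseline and "after the 16-week intervention (week 16) and at the end of the follow-up period (week 32), transvaginal ultrasound examinations will be performed". No visit is ranked above another.
- **Section 2.8, Sample size estimation.** Here the endpoint is specific: "The sample size was calculated based on the primary outcome, namely the change in AFC from baseline to week 16". The calculation gives 28 per group, raised to 33 for 15% dropout.

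**The concern.** There are two linked issues.

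The first is precision. If week 0 enters the model as a response with a free group effect, the group × week-16 term is the difference between arms in mean change. Subtracting baseline is not the same as adjusting for it. Unless baseline and follow-up are almost perfectly correlated, the change score carries baseline noise that a covariate or a constrained baseline would remove. In a 66-participant trial that already collects baseline AFC, that precision is given up for nothing.

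The second is which test decides the trial. Over three visits the overall group × time test has 2 degrees of freedom and asks whether the arms differ in change at week 16, week 32 or both. The trial was sized on a single 1-degree-of-freedom comparison at week 16. Because sections 2.7.1 and 2.9 do not repeat the week-16 choice made in section 2.8, a reader of the results could not tell from the analysis text which p-value was meant to be decisive.

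**Working it through.** **Inputs from section 2.8.** "the mean AFC level after YYRM treatment in the intervention group was 4.16 ± 0.86"; "the change in the waitlist group was 3.00 ± 1.69"; one-sided alpha 0.025 (equivalent here to two-sided 0.05); power 90%; 28 per group. The root-mean-square SD is sqrt((0.86² + 1.69²)/2) = 1.341.

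**Reproducing the plan's figure.** n per arm = 2 × (SD × (1.960 + 1.282)/difference)².

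- Difference 4.16 − 3.00 = 1.16: n = 28.08. This matches the stated 28, and 28/0.85 rounds up to 33.
- The stated difference ("Assuming a minimal clinically important difference of 1.8 between the two groups"): n = 11.7, that is 12 per arm. This does not reproduce 28.

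The figures below therefore use 1.16. The sizing corresponds to an unadjusted two-sample comparison. At 28 per arm its power is 89.9% by the normal approximation and 88.9% by the t-test (54 degrees of freedom). The rest uses the t-test.

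**Variance comparison**, assuming the same SD s at both visits and baseline-to-week-16 correlation rho:

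- Difference in change: variance proportional to 2s²(1 − rho).
- Baseline-adjusted: variance proportional to s²(1 − rho²).
- Ratio, adjusted to change: (1 + rho)/2.

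The protocol gives no rho, so 0.3, 0.5 and 0.7 are assumptions. The ratio is 0.65, 0.75 and 0.85; equivalently, the change analysis has 1.54, 1.33 and 1.18 times the variance.

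**Power at 28 per arm, difference 1.16.** Section 2.8 describes one input as a level and the other as a change, so both readings of the 1.341 are shown.

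| rho (assumed) | SD of change: unadjusted | SD of change: adjusted | SD of levels: unadjusted change | SD of levels: adjusted |
|---|---|---|---|---|
| 0.3 | 89% | 98% | 77% | 92% |
| 0.5 | 89% | 96% | 89% | 96% |
| 0.7 | 89% | 93% | 98% | 99% |

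The SDs used are 1.341 and 1.341 × sqrt((1 + rho)/2) in the first pair, and 1.341 × sqrt(2(1 − rho)) and 1.341 × sqrt(1 − rho²) in the second.

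**Does the model contain the week-16 change?** Yes, on the natural reading. In a simulated complete data set with a random intercept and categorical time, the group × week-16 coefficient and the raw difference in mean change were both 1.2119. The contrast can be estimated; it is not named as the primary test.

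**If either visit could be claimed.** With the week-16 and week-32 contrasts each tested at two-sided 5%, the chance of at least one false positive is 9.1% at a contrast correlation of 0.5 and 7.8% at 0.8. This applies only under that decision rule, which the protocol does not state.

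**The case against.** The strongest reply is that nothing here is invalid. Under randomisation the difference in change is unbiased, the trial was sized without adjustment, and section 2.8 does name week-16 change as the primary outcome. An article may also leave covariates, time coding and the exact contrast to an analysis plan that is not shown. Most of this stands. It limits the point to an efficiency gain and a missing link between sections. It does not remove the point, because section 2.9 goes as far as listing the fixed effects and that list omits baseline AFC.

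Four stronger readings might be inferred, and the document does not support them.

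- **That the trial has two primary endpoints.** Section 2.7.1 gives a measurement schedule, and section 2.7.2 uses the same visits for secondary outcomes. Nothing says success at either visit would count.
- **That the model cannot isolate the week-16 change.** As shown, it contains that contrast.
- **That the 2-degree-of-freedom test necessarily costs power.** It depends on week 32. With a contrast correlation of 0.5 (compound symmetry) and 1.341 as an SD of change, joint-test power is 91% if the week-32 effect is zero or equal to the week-16 effect, against 89% for the single contrast. It is 81% if the week-32 effect is half as large. The objection to the joint test is that it answers a different question.
- **That planned power is lost.** The loss is relative to a better analysis. Power falls materially below the planned 90% for this reason only if the SDs are SDs of levels and rho is below about 0.5.

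The model and its responses are also not labelled as primary; that is the natural reading of section 2.9, not its wording.

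**Conclusion.** The point holds as an efficiency and clarity matter. As listed, the model's week-16 contrast is valid but unadjusted. Adjusting for baseline AFC would cut its variance by 15% to 35% for rho between 0.7 and 0.3, given equal SDs at the two visits. In power that is a gain of about 4 to 9 points if 1.34 is an SD of change, and about 1 to 15 points if it is an SD of levels. These sizes rest on an assumed rho, on 28 evaluable per arm, and on a difference of 1.16 in place of the stated 1.8; that discrepancy in section 2.8 is a separate matter.

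Sections 2.7.1 and 2.9 also need to carry over the week-16 primary outcome that section 2.8 already fixes, since the overall group × time test is not the comparison that was sized. No bias and no inflated error rate is shown in the plan as written.

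**What to change.** - **Section 2.9, model.** Take AFC at weeks 16 and 32 as the responses, with baseline AFC (and its interaction with time), group, time and group × time as fixed effects. A constrained-baseline model, with week 0 as a response and equal baseline means across arms, is an acceptable alternative.
- **Section 2.9, primary test.** Name the 1-degree-of-freedom adjusted group difference in AFC at week 16, two-sided 5%, as the sole primary test.
- **Section 2.7.1.** State that week 16 is the primary time point and list week-32 AFC as secondary.
- **Other continuous outcomes.** Use the same baseline-adjusted form for AMH, FSH, LH and the symptom, mood and quality-of-life scales.

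The cost is wording only. Baseline values are already collected, no visit or sample-size change is needed, and enrolment is expected to run to December 2027, so the change can be fixed and dated before any comparative analysis.
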